#### Phase II/2

In the 2^nd^ stage, the patients will be allocated in the ratio of 2:2:1:1, 2 for each active arm and 1 for each PbO, and the same statistic will be used as in Phase II/1. Details are described in the Statistical Analysis Plan - SAP (Supplementary material 2).

As in Phase II/1, the interim analysis planned after inclusion and data are collected from half of the planned patients will only assess safety data.

#### Phase III

The third stage of the study will proceed in a 2:1 allocation (two active treatments for each PbO), with a minimum inclusion of 189 patients and a maximum of 564. The study will perform interim analyses that may interrupt the study due to safety, futility, or efficacy, using all participants already randomized in Phases II/1 and II/2, since the primary efficacy outcome of Phase III (time of use of ventilatory support within 15 days) will be analyzed for all patients from these earlier phases as well.

The hypothesis test for the treatment effect will be performed using a generalized additive model of location and scale considering the distribution of a beta-binomial mixture with inflated zeros for the data adjusted by age and considering the random effect of the center for each intercept (model for the beta-binomial part and for the probability of zeros).

Phase III has three interim analyses planned, m = 3, for each third of the collected sample. The interim analyses consider stop limits according to the O’Brien-Fleming criterion, with significance levels of 0.06%, 1.51% and 4.71%, respectively, to maintain the global significance level at 5%. In Phase III, discontinuations due to futility will be allowed and use the same stopping criteria defined for efficacy.

Although the PbO group is composed of individuals receiving PbOs for three separate drugs (sometimes in combination), it will always be evaluated as a single group after gathering information from all “PbO arms”.

Secondary/exploratory outcomes and additional analyses are described in Supplementary material 1 (Section S4.1).

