### Sample size

We intend to include 252 patients in Phase II/Stage 1 (189 in the active groups and 63 in the PbO group) and 189 patients in Phase II/Stage 2 (126 in the active groups and 63 in the PbO group). For Phase III, 564 additional participants will be randomized (376 in the active group and 188 in the PbO group). Thus, at the end of Phase III, 314 patients will have been evaluated in the PbO group and between 439 and 502 patients will have been evaluated in the treatment group if the study persists through the three phases. More details about the sample size calculation are described in Supplementary material 2 (Statistical Analysis Plan).

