### Statistical methods

The main analysis of the data from this study will be performed on patients of the intention-to-treat (ITT) population. The definition of the analysis populations and more details on statistical methods are available in the Statistical Analysis Plan. The analyses will be performed with R software (R Core Team, 2020).

All the different PbOs for ATV, DCV and SOF will always be analyzed together as a single PbO group.

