### Analysis of primary outcomes

#### Phase II/1

In Phase II/1, patients will be allocated in ratio of 3:3:3:1:1:1 (3 for each treatment group and 1 for PbO). For Phase II/1, the parameter of interest for the decision will be the comparison of the decay rates of the viral load logarithm from real time polymerase chain reaction (RTPCR) to COVID-19 in 9 days between the treatment groups compared with the control using a mixed linear model.

The interim analysis, which is planned to begin when 126 patients are randomized and followed for at least 10 days, will be exclusively conducted for a patient safety assessment (based on safety outcomes and adverse events).

At the end of Phase II/1, each group will be compared with the PbO group considering a significance level for each comparison of 0.067 (Bonferroni correction for multiple comparisons), such that the global type I error of Phase II/1 will be 0.20. If no treatment is significantly different from the PbO group at the stipulated level of significance, the study will be terminated at this stage.

Among the treatments significantly different from the PbO group in relation to the linear rate of viral load decay, the one with the highest rate of decay and considered safe by the independent study safety committee will be a candidate treatment for inclusion in Phase II/2 of the study. It will be combined with the drug responsible for the second highest linear decay rate to comprise the second Phase II/2 treatment group.

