## DISCUSSION

This manuscript describes the protocol of the REVOLUTIOn trial, which is a randomized, PbO-controlled, adaptive, multiarm, multistage study to evaluate the efficacy of ATV, DCV and SOF simultaneously compared with their PbOs. The main objective is to identify whether any of these drugs alone or in combination are capable of reducing viral load and, if so, investigate the clinical outcome of increasing the number of days free of respiratory support in a larger population.

Expeditious and methodologically rigid clinical trials are demanding to identify safe and effective treatments. Nevertheless, rapid identification and abandonment of harmful or ineffective approaches are equally important, especially during a pandemic. The principal aim of the REVOLUTIOn trial is to aid in the recognition of any of these 3 repurposed antivirals as treatments for COVID-19. The multiarm, multistage design of REVOLUTIOn helps rapidly identify the effectiveness of these drugs in a seamless manner and at the same time, starting with a Phase II clinical trial focusing on safety and ending with a Phase III trial capable of answering clinically important questions.

Repurposed drugs are important in resource-limited settings because the interventions are more rapidly available, have already been tested safely in other populations and are inexpensive.

Limitations of the protocol are described below. First, decisions related to changing stages rely on a decreasing viral load in the initial phases despite extensive debate on the association of viral load with worse clinical outcomes.^(12)^ Second, late initiation in recruiting participants in the pandemic timeline slowed our recruitment rate, as pandemic cases steadily decreased after vaccination outset and, third, late protocol publication, although the content of this protocol paper is absolutely consistent with the protocol submitted and approved by the national/local Ethics Research Committee, our national regulatory agency (Anvisa) and ClinicalTrials.gov.

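### As stated, the Phase III primary test pools Phase II patients randomised at a different ratio and names no stage term, so a difference in mean outcome between stages biases the treatment effect

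*Protocol article*

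**What the plan says.** The Phase III section states that the interim analyses are performed "using all participants already randomized in Phases II/1 and II/2", and that the Phase III primary outcome "will be analyzed for all patients from these earlier phases as well". The Sample size section carries the pooling through to the final analysis, giving the placebo total first and then the range for active treatment: "at the end of Phase III, 314 patients will have been evaluated in the PbO group and between 439 and 502 patients". Phase III itself randomises only 188 placebo and 376 active patients, so those totals are reached only by adding Phase II patients.

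Placebo is one group throughout: "All the different PbOs for ATV, DCV and SOF will always be analyzed together as a single PbO group".

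The allocation changes by stage. The first stage is described thus: "patients will be allocated in ratio of 3:3:3:1:1:1 (3 for each treatment group and 1 for PbO"). For the second, "the patients will be allocated in the ratio of 2:2:1:1, 2 for each active arm and 1 for each PbO". In Phase III it is 2:1, active to placebo.

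The model for the Phase III test is a zero-inflated beta-binomial, "adjusted by age and considering the random effect of the center for each intercept". The article names no term for stage or calendar period, and no restriction to placebo patients randomised at the same time as the selected arm.

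**The concern.** Randomisation protects a comparison within a stage. When stages with different allocation ratios are merged and stage is left out of the model, the two arms hold different mixtures of stages. A difference in mean days free of respiratory support between stages then appears as a treatment effect. The random centre intercept does not remove a change over time within a centre.

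The exposed path is the one on which the combination first formed in Phase II/2 goes forward. That arm has no Phase II/1 patients, so all 63 Phase II/1 placebo patients are non-concurrent controls. At stake is the confirmatory test of the clinical endpoint and the overall 5% level that the article claims for it.

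**Working it through.** **Inputs.** Stage sizes and totals are from the Sample size section. Ratios are from Sequence allocation and the three phase sections. The three-look levels of 0.06%, 1.51% and 4.71% are from the Phase III section.

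**Reproducing the plan's figures.**
- II/1: 252 × 3/12 = 63 per active arm; pooled placebo 252 × 3/12 = 63.
- II/2: 189 × 2/6 = 63 per active arm; pooled placebo 189 × 2/6 = 63.
- III: 564 × 4/6 = 376 active; 564 × 2/6 = 188 placebo.
- Placebo total 63 + 63 + 188 = 314. Active total 376 + 63 = 439 or 376 + 126 = 502. Maximum 252 + 189 + 564 = 1,005.

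All agree with the article.

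**Bias formula.** Let d be the Phase III mean minus the Phase II mean, with the II/1 and II/2 means taken as equal. With no true effect and no stage term, the expected difference between arms is

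bias = d × (Phase II share of placebo − Phase II share of active).

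| Path | Share of placebo | Share of active | Bias / d |
|---|---|---|---|
| Single drug, all stages | 126/314 = 40.1% | 126/502 = 25.1% | 0.1503 |
| II/2 combination selected | 126/314 = 40.1% | 63/439 = 14.4% | 0.2578 |
| II/2 skipped | 63/251 = 25.1% | 63/439 = 14.4% | 0.1075 |

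On the combination path, 63/314 = 0.2006 of the coefficient comes from the II/1 placebo patients and 63/314 − 63/439 = 0.0571 from II/2. At the first Phase III look (one third of 564) the coefficients are larger: 0.167, 0.333 and 0.167.

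**Effect on type I error.** The shift in Z at the final analysis is bias / √(1/nA + 1/nP), in SD units. For d = 0.2 SD:
- single drug: 0.0301 / 0.0719 = 0.418
- combination: 0.0516 / 0.0739 = 0.698
- II/2 skipped: 0.0215 / 0.0791 = 0.272

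A simulation of the three looks at the stated levels (two-sided assumed, 400,000 replicates, difference in means in place of the zero-inflated model, age and centre ignored) gave these overall type I error rates:

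| Assumed d | Single drug | Combination | II/2 skipped |
|---|---|---|---|
| 0 | 5.0% | 5.1% | 5.1% |
| 0.1 SD | 5.4% | 6.5% | 5.3% |
| 0.2 SD | 6.9% | 10.8% | 5.9% |
| 0.3 SD | 9.4% | 18.1% | 7.0% |
| 0.5 SD | 16.9% | 40.7% | 10.1% |

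With the comparison stratified by stage, the error stayed between 4.9% and 5.2% in every case.

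**Information cost of stratifying.** Pooled information is nA·nP/(nA + nP). Stratified information is the sum of the same expression over stages that contain both arms: 31.5 for each Phase II stage (63·63/126) and 125.3 for Phase III (376·188/564).
- Single drug: 188.3 against 193.2, a loss of 2.5%.
- Combination: 156.8 against 183.1, a loss of 14.3%.
- II/2 skipped: 156.8 against 159.7, a loss of 1.8%.

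On the combination path, removing the 63 non-concurrent placebo patients alone takes 183.1 to 159.7, which is most of the loss.

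**The case against.** The strongest objection is that the SAP is not shown. The article refers the reader to it for statistical detail, and it may name a stage term. That stands as a limit: the point concerns the model as the article states it. It does not dispose of the point, because the article gives the distribution, the covariate, the random effect and the parts of the model they enter. If the SAP adds stage, the article's statement needs correcting.

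Second, a reader might infer that the documents show outcomes drifting over time. They do not. The Discussion's remark that "pandemic cases steadily decreased after vaccination outset" explains slow recruitment. The section on daily routines leaves corticosteroids, IL-6 inhibitors and other antivirals to the attending physician without saying that practice changes. Some features favour stability: one set of eligibility criteria for all stages, and a drug-interaction table that has all patients on dexamethasone. What the documents do support is plausibility. Table 5 spans April 2021 to March 2022; 256 patients, about the II/1 target, were randomised by July 2021, so later stages fall in a later period; and blinding is partial in Phase II but global in Phase III.

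Third, a reader might conclude that any calendar trend biases the result. That is too broad. Drift within a stage at a constant ratio does not bias the contrast; only a difference in mean between stages does.

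Fourth, the large figures need a chain of events: II/2 is run, its combination is chosen, and stage means differ materially. On the other two paths the inflation at 0.2 SD is at most about 2 percentage points. This is fair.

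**Conclusion.** The point holds for the model as the article states it. Stage is associated with treatment by design, and the named terms do not adjust for it. The treatment effect absorbs 0.150 (single drug), 0.258 (combination) or 0.107 (II/2 skipped) of any difference in mean outcome between Phase II and Phase III. For assumed differences of 0.1 to 0.3 SD, overall type I error is 5.4% to 9.4%, 6.5% to 18.1% and 5.3% to 7.0% respectively.

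It would go too far to say that the 5% level is lost. It is lost only if stage means differ, and the documents neither show nor rule out such a difference. If outcomes improve over time the bias favours the drug; if they worsen it runs against it. The figures rest on equal II/1 and II/2 means, a two-sided test (the article does not state sidedness), and a difference-in-means approximation. The non-concurrent placebo patients on the combination path are the main exposure.

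**What to change.** Add stage (II/1, II/2, III) as a fixed effect in both parts of the Phase III model, the beta-binomial mean and the probability of zero, and use that model at every Phase III look as well as at the end. State that on the II/2-combination path the 63 II/1 placebo patients are non-concurrent and add essentially no information to the treatment contrast. If the SAP already specifies this, bring the article's model statement into line with it.

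The cost is one factor in each part of the model and the information losses derived above: about 2.5% (single drug), 1.8% (II/2 skipped) or 14% (combination). Most of the 14% comes from controls that randomisation does not protect, so the 314 placebo patients should not be counted in full towards precision on that path.

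### Phase III pools the clinical outcomes of the arm selected on Phase II viral decay at levels that correct only for repeated looks, so the efficacy-direction error can modestly exceed 2.5% once Phase III is reached

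*Protocol article*

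**What the plan says.** **Selection.** Under Phase II/1 in the protocol article, each active arm is compared with pooled placebo on viral decay at 0.067. Among the significant arms, "the one with the highest rate of decay and considered safe by the independent study safety committee" becomes the candidate to go forward. The rules for changing the study stage then send the arm with the highest decay rate in Phase II/1 or II/2 into Phase III.

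**Reuse.** Under Phase III, the analyses are done "using all participants already randomized in Phases II/1 and II/2", on the ground that the Phase III primary outcome is also recorded in the earlier phases. The Sample size section confirms the pooling through its final group sizes of 314 on placebo and 439 to 502 on treatment.

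**Error claim.** "Phase III has three interim analyses planned, m = 3, for each third of the collected sample", "with significance levels of 0.06%, 1.51% and 4.71%, respectively, to maintain the global significance level at 5" per cent. Sidedness is not stated. The text adds that "discontinuations due to futility will be allowed and use the same stopping criteria defined for efficacy". The 5% is taken here as two-sided, that is, 2.5% in the direction of benefit.

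**The concern.** The three levels account for testing the same comparison three times. They do not account for choosing the arm, or for requiring it to beat placebo, on an endpoint measured in patients whose clinical outcomes are then counted again. Selection favours an arm whose Phase II patients happened to do well and a placebo group that happened to do badly. If viral decay and respiratory-support days are correlated within patients, part of that luck enters the confirmatory comparison.

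What is at stake is the probability of declaring benefit for a drug that clears virus but does not help patients. Phase III exists to exclude exactly that false positive. The effect estimate is also pushed slightly upward.

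**Working it through.** **1. The plan's own figures.**
- Phase II/1 threshold: 0.20/3 = 0.067. Reproduced.
- Pooled groups: 63 + 376 = 439; 63 + 63 + 376 = 502; placebo 63 + 63 + 188 = 314. Reproduced, so Phase II patients of the selected arm and of placebo are counted in Phase III.
- Levels 0.06%, 1.51% and 4.71% correspond to z = 3.432, 2.430 and 1.985. At equal thirds their joint two-sided error is 5.24% by trivariate normal integration. With Phase II data added, the looks fall at information fractions of about 0.47-0.56, 0.74-0.78 and 1, and the error is 5.02-5.10%. Without selection, each direction is therefore 2.51-2.55%. The levels do what is claimed for repeated looks, and nothing in them is left over for selection.

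**2. Hand check of the mechanism.** Take Phase II/2 as skipped, so the pooled comparison is 439 v 251 (63 + 188). Suppose all three drugs lower viral load so strongly that Phase III is always reached. Outcomes are in SD units and there is no clinical effect.
- Expected excess of the best of three arm means: 0.846/√63 = 0.107 SD on viral decay.
- Carried into the pooled clinical mean: rho × 0.107 × 63/439. At rho 0.3 this is 0.0046 SD; at rho 0.5, 0.0076 SD.
- Standard error: √(1/439 + 1/251) = 0.079 SD. The shifts are 0.058 and 0.097 standard errors.
- Upper-tail error, approximately: 1 − Φ(1.96 − 0.058) = 2.9%; 1 − Φ(1.96 − 0.097) = 3.1%.

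**3. Simulation.** At least 1 million trials per setting. Inputs: 63 patients in each of three active arms and 63 on placebo; best arm on viral decay, going forward if better than placebo at two-sided 0.067; no clinical effect; pooled 439 v 251; one look at two-sided 5%. A normal statistic stands in for the beta-binomial model. Rho and the viral effect (equal in all arms) are assumptions.

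| Viral effect | Reach Phase III | rho | Error for benefit, given Phase III | Error for benefit, all trials |
|---|---|---|---|---|
| none | 8% | 0.3 | 4.7% | 0.4% |
| none | 8% | 0.5 | 6.6% | 0.5% |
| 0.3 SD | 69% | 0.3 | 3.2% | 2.2% |
| 0.3 SD | 69% | 0.5 | 3.7-3.8% | 2.6% |
| 0.5 SD | 96% | 0.3 | 2.9% | 2.8% |
| 0.5 SD | 96% | 0.5 | 3.1-3.2% | 3.0% |
| 1 SD | 100% | 0.3 | 2.8-2.9% | 2.8-2.9% |
| 1 SD | 100% | 0.5 | 3.1% | 3.1% |

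The 1 SD rows agree with the hand check. At rho 0 selection adds nothing.

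**4. Three looks.** At 0.3 SD, the error given Phase III becomes 3.3% (rho 0.3) and 3.9% (rho 0.5), about 0.1 point more than with one look. If Phase II/2 is run, a 1 SD effect with three looks gives 3.0% at rho 0.3 and 3.2-3.3% at rho 0.5.

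**5. Other tail and estimate.** At 0.3 SD and rho 0.3 the harm tail falls to 1.8%, so the two-sided total is 3.2 + 1.8 = 5.0%. At 1 SD, rho 0.3 and three looks it is 2.9 + 2.2 = 5.1%. Upward bias at rho 0.3 is about 0.005 SD (0.5-1 SD viral effect) to 0.01 SD (0.3 SD).

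**The case against.** Four points on the other side carry weight.

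- **The stated 5% is roughly kept.** A reader might infer that the claim "to maintain the global significance level at 5" per cent is materially breached. The documents do not support that: the two-sided total stays near 5%, and the 2.5% per direction is itself inferred. What remains is a shift between the tails, and only the enlarged one supports an efficacy claim.
- **The excess is not universal.** A reader might infer that the whole-trial false-positive rate for benefit always exceeds 2.5%. It does not. At a 0.3 SD viral effect, 31% of trials stop in Phase II and the whole-trial error is 2.2% at rho 0.3. With no viral effect it stays below 1% for rho up to 0.7 (1.2% at rho 1). The excess holds given Phase III, and over all trials when the viral effect is large enough that most trials proceed.
- **Rho is unknown.** It would be tempting to call a positive correlation the premise of the trial. The premise is that a drug effect on viral load may carry over to clinical benefit, whereas the excess depends on correlation between patients within an arm. The Discussion calls the association of viral load with outcome debated.
- **The SAP (Supplementary material 2) is not shown** and may report operating characteristics. That does not remove the point, because the article itself fixes the levels and says what they achieve.

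**Conclusion.** The point holds, at modest size. Selection on Phase II viral decay, combined with reuse of the same patients' clinical outcomes, is not covered by levels that allow only for repeated looks. For any positive rho, a drug that lowers viral load without clinical benefit has an efficacy-direction error above 2.5% once Phase III is reached. Over the assumed rho of 0.3 to 0.5 that error is roughly 2.9% to 3.8%, depending mainly on how close the viral effect lies to the Phase II threshold, plus about 0.1 point for the three looks. The whole-trial error runs from 2.2% to 3.1% for viral effects of 0.3 to 1 SD.

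This rests on a two-sided reading of the 5%, equal viral effects in all arms, a normal approximation and an assumed rho. Confidence is high in the direction and medium in the size. It should be corrected, but it is no ground for discarding the pooled design.

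**What to change.** Keep the pooled data. Before the first Phase III look:

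1. Simulate the efficacy-direction error under the actual selection rule, with and without Phase II/2, with the three looks at their true information fractions and the planned model, over a range of rho and viral effects that includes none. Report it both given Phase III and over all trials.
2. Either calibrate the efficacy boundary so that the error is 2.5% over that range, or state the simulated error in place of the claim that the levels maintain 5%. Do not take a boundary from one assumed scenario, because the required value changes with rho, the viral effect and the looks.
3. Report the comparison in Phase III patients only as a sensitivity analysis. Selection has no effect on it.

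The cost is simulation and wording, plus a slightly stricter boundary or a slightly less favourable stated error. Recruitment does not change. Making Phase III-only the main analysis would cost more. It keeps 125.3/159.7 = 78% of the information when Phase II/2 is skipped (376 × 188/564 against 439 × 251/690), so an effect with 80% power in the pooled analysis would have Φ(2.80 × √0.785 − 1.96) = 70%.

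### The printed Phase III O'Brien-Fleming levels slightly overspend 5% at equal thirds and are not O'Brien-Fleming levels at the information the pooled looks will hold

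*Protocol article*

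**What the plan says.** The Phase III paragraphs of the protocol article (Analysis of primary outcomes) fix the stopping rule in four statements:

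- Schedule: "Phase III has three interim analyses planned, m = 3, for each third of the collected sample".
- Boundary: "The interim analyses consider stop limits according to the O’Brien-Fleming criterion".
- Levels and purpose: "significance levels of 0.06%, 1.51% and 4.71%, respectively, to maintain the global significance level at 5" (per cent). Sidedness is not given.
- Data at each look: "using all participants already randomized in Phases II/1 and II/2", because the Phase III outcome is also analysed in those patients.

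The same section sets Phase III recruitment "with a minimum inclusion of 189 patients and a maximum of 564". The Sample size section says that "564 additional participants will be randomized (376 in the active group and 188 in the PbO group"). It gives the final pooled sample as 314 on placebo and 439 to 502 on active treatment if all three stages run.

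**The concern.** Two things do not fit.

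First, the three levels look like an O'Brien-Fleming boundary for equally spaced looks, but with a constant too small to hold 5% overall.

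Second, equal spacing is not what the section describes. If every look includes the Phase II patients, the first look already holds well over a third of the final information. A boundary indexed to thirds is then not O'Brien-Fleming for this trial.

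At stake are the exact global error that the section promises and the chance that an effective drug is recognised at the first look. The article gives rapid identification of effective drugs as a reason for the design.

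**Working it through.** **Inputs.** Nominal levels 0.0006, 0.0151 and 0.0471, and global level 0.05 (Phase III). Phase III adds 376 active and 188 placebo patients. Phase II/1 has 189/3 = 63 per active arm and 63 placebo; Phase II/2 has 126/2 = 63 per active arm and 63 placebo (Sample size). The third look, at the last third, is taken as the final analysis. Testing is assumed two-sided unless stated.

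**Step 1: the plan's own figure at equal thirds.** The two-sided levels correspond to z = 3.432, 2.430 and 1.985. An O'Brien-Fleming boundary has z_k = C/√t_k, so C = z_k√t_k. With t = 1/3, 2/3 and 1 this gives 1.981, 1.984 and 1.985. The shape is right, with C about 1.985.

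Overall error = 1 − P(|Z_k| < z_k at every look), where corr(Z_i, Z_j) = √(t_i/t_j) for i < j. Numerical integration gives **5.24%**; rounding of the printed levels moves this only between 5.23% and 5.25%. Simulation of 8 million trials also gives 5.24%. If the levels are one-sided, the result is 5.14%. The stated 5% is not reproduced. Solving for exactly 5% gives C = 2.004 and levels of **0.052%, 1.41% and 4.51%**. O'Brien-Fleming-type (Lan-DeMets) spending at thirds gives 0.021%, 1.20% and 4.63%. No standard one- or two-sided variant tried reproduces all three printed levels.

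**Step 2: where the looks fall.** 564/3 = 188, which agrees with the minimum of 189, so the thirds appear to be thirds of the new patients. Information for a two-group comparison is I = nA·nP/(nA + nP). At look k, nA = a + 376k/3 and nP = p + 188k/3, where a and p are the patients carried over.

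| Case | a, p | I at looks 1, 2, 3 | Fraction of final |
|---|---|---|---|
| Combination selected | 63, 126 | 94.2, 139.5, 183.1 | 0.515, 0.762, 1 |
| Single drug carried through both stages | 126, 126 | 107.8, 150.7, 193.2 | 0.558, 0.780, 1 |
| Phase II/2 skipped | 63, 63 | 75.4, 117.7, 159.7 | 0.472, 0.737, 1 |

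For example, in the combination case look 1 has 188.3 × 188.7/377 = 94.2, the final analysis has 439 × 314/753 = 183.1, and the ratio is 0.515.

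**Step 3: error and matching levels at those fractions.**

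| Case | Error with printed levels, two-sided (one-sided) | Exact O'Brien-Fleming levels | Lan-DeMets levels |
|---|---|---|---|
| Combination | 5.05% (4.97%) | 0.47, 2.03, 4.27% | 0.36, 1.94, 4.36% |
| Single drug | 5.02% (4.94%) | 0.65, 2.14, 4.21% | 0.54, 2.07, 4.30% |
| II/2 skipped | 5.10% (5.02%) | 0.33, 1.86, 4.33% | 0.22, 1.73, 4.44% |

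The error is lower than at thirds because the looks are more highly correlated. The printed first look is 0.33/0.06 = 5.5 to 0.65/0.06 = 10.8 times stricter than exact O'Brien-Fleming.

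**Step 4: what this does to early stopping.** The documents give no Phase III power, so 90% overall is assumed. In the combination case, the chance of stopping for efficacy at look 1 is about 14% with the printed levels and 31% with exact O'Brien-Fleming levels. By look 2 the cumulative chances are about 66% and 70%. Overall power falls by under half a percentage point.

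**Step 5: the other reading of the thirds.** If the collected sample means the pooled total, look 1 needs 753/3 − 189 = 62 new patients (combination), 816/3 − 252 = 20 (single drug) or 690/3 − 126 = 104 (II/2 skipped). All three conflict with the minimum of 189. On that reading the looks would be near equal thirds, and the 5.24% from step 1 would apply.

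**The case against.** The strongest reply is that the two halves cannot both bite. If the looks are at pooled fractions, 5.24% is not this design's error. The excess is then 0.02 to 0.10 percentage points, which is small against the approximation used to compute it, and nothing material if the levels are one-sided. This stands, and it limits the point.

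A reader might also infer that 4.71% at the end is too lenient for the pooled design. The documents do not support that. A boundary need not have the O'Brien-Fleming shape to control error, and the strict first look largely pays for the final level. Only at equal thirds is 4.51% a true correction of 4.71%.

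A strict first look is conservative, and its cost shrinks by the second look. The early-stopping figures also rest on an assumed power. Both remarks are fair.

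The information fractions come from patient counts, whereas the planned model is a zero-inflated beta-binomial adjusted for age with random centre effects. They are approximate, which is a reason to measure information at each look.

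Finally, the article refers detail to the statistical analysis plan, which is not shown and may recompute the levels. But the article itself prints the levels and the purpose they serve, and under neither sidedness do they give 5% at thirds.

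**Conclusion.** The point holds in a limited form. As printed, the levels give 5.24% two-sided (5.14% one-sided) at equal thirds, an excess of about 0.24 points (0.14 one-sided) over the stated 5%. On the more natural reading of the section, with Phase II pooled and looks at thirds of the 564 new patients, they are not O'Brien-Fleming levels for the design. The first look is set at 0.06%, where the criterion would give about 0.33-0.65%.

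It would be tempting to conclude that the two defects compound and that the trial runs with a materially inflated error. They do not compound: at the pooled fractions the two-sided error is about 5.02-5.10%. The practical effect there is a lower chance of stopping early for an effective drug.

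This rests on two-sided testing where not otherwise stated, a normal approximation to information, full planned enrolment at each stage, and Phase II data treated as unselected. Any effect of choosing the best arm before pooling is a separate matter and is not in these figures. The correction is worth making before any Phase III look because it concerns a decision threshold and changes mainly wording.

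**What to change.** State whether the levels are one- or two-sided, and whether the thirds refer to new Phase III patients or to the pooled sample. Replace the three fixed levels with an O'Brien-Fleming-type alpha-spending function evaluated at the information actually available from the pooled model at each look. This holds 5% whichever stages are run and whatever the exact timing. If looks at fixed thirds of information are kept, print 0.05%, 1.41% and 4.51% (two-sided). Carry the same text into the statistical analysis plan and the DSMB charter.

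The cost is wording, a final-look level of about 4.2-4.5% in place of 4.71%, and less than half a percentage point of power. No patients need be added for this alone.
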